**CONMED**^g^	Current medication use [70]	Yes (type, dosage)/No	Baseline
**HRSD-17**^e,g^	Severity of depression [71]	Score range: 0–53 (0–7 no depression; 8–13, mild depression; 14–18 moderate depression; 19–22, severe depression; ≥ 23 very severe depression)	Baseline, end of week 2 and 4 (and final week of additional treatment for non-remitters^d^); beginning of maintenance weeks 1–13, 15, 17, 19, 21, and final visit (week 24)
**MADRS**^f,g^	Severity of depression [72]	Score range: 0–60 (0–6, absence of symptoms; 7–19, mild depression; 20–34, moderate depression; 35–60, severe depression)	Baseline, end of week 4 (and final week of additional treatment for non-remitters^d^); final visit (week 24)
**SRRS**^g^	Depression-related psychomotor impairments [73]	Score range: 0–60	Baseline, end of week 4 (and final week of additional treatment for non-remitters^d^); final visit (week 24)
**YMRS**^f,g^	Presence and severity of manic or hypomanic symptoms [74, 75]	Score range: 0–60 (2, euthymia; 3, depression; 12, mania)	Baseline, end of week 2 and 4 (and final week of additional treatment for non-remitters^d^); beginning of maintenance weeks 1–13, 15, 17, 19, 21, and final visit (week 24)
**C-SSRS**^a,g^	Quantify suicidal ideation and behaviour [76]	5 items rated yes or no, with additional clarifying questions	Baseline and end of weeks 1–4 (and both weeks of additional treatment for non-remitters^d^); beginning of maintenance weeks 1–13, 15, 17, 19, 21, and final visit (week 24)
**MMSE**^b,^^g^	Presence of dementia [77]	Score range: 0–30 (30–26, could be normal; 25–20, mild; 19–10, moderate; 9–0, severe)	Screening visit
**Physician consultation**^g^	Verify general suitability for TBS; clinical oversight	N/A	Before participants consent to the study, end of week 4 (or final week of additional treatment for non-remitters^d^), end of maintenance, and/or as needed throughout the study
**QIDS-SR**_**16**_^f^	Depressive symptoms [78]	Score range: 0–27 (0–5, no depression; 6–10, mild depression; 11–15 moderate depression; 16–20 severe depression; ≥ 21, very severe depression)	Baseline, end of weeks 1–4 (and both weeks of additional treatment for non-remitters^d^); beginning of maintenance weeks 1–13, 15, 17, 19, 21, and final visit (week 24)

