The TBS treatment will be administered by trained research personnel 5 days a week (Monday-Friday) over the first 4 weeks (initial treatment phase; Fig. 2B). Participants who do not achieve remission (i.e., non-remitters) after the initial treatment phase as per the 17-item Hamilton Rating Scale for Depression (HRSD-17; score of > 7) will undergo two additional weeks of treatment (totaling 6 weeks of initial treatment) (Fig. 2C). The additional two weeks provides an opportunity for individuals, particularly older adults, who require a longer period to achieve response from stimulation treatments [89]. Participants who do not respond to treatment (i.e., < 50% decrease in pre-treatment HRSD-17 score) after the two additional weeks of full treatment will be discharged from the study and treatment recommendations will be provided to their referring physician by the study psychiatrist. Participants who show remission at week 4 or response at week 6 will enter a six-month maintenance phase, where treatment will be determined based on their symptomatology (Fig. 2D and E). In the first 4 weeks of this phase, participants will be remotely assessed for clinical outcomes (phone or video-call) once per week (e.g., on Mondays) and treatment will be administered 2x/week (e.g., every Wednesday and Friday). In the following 8 weeks (i.e., weeks 9–16) treatment frequency will be further decreased, and the HRSD-17 score, remotely assessed weekly on Mondays, will determine the number of treatment sessions that week. Participants can receive 0, 1, or 2 treatment sessions, as follows: a) no TBS session, if HRSD-17 score of ≤ 8 (no depression) or a < 3 point increase from their final initial treatment HRSD-17 score; b) 1 TBS session, if their HRSD-17 score increased by ≥ 3 and < 8 from their final initial treatment HRSD-17 score; c) 2 TBS sessions, if their HRSD-17 score increased by ≥ 8 from their final initial treatment HRSD-17 score [60]. From week 17–25, participants will be clinically assessed on Mondays of every second week to determine whether they will receive 0, 1, or 2 TBS sessions that week based on the same criteria previously mentioned. Finally, in week 28 participants will complete clinical assessments and TMS-EEG on Monday and Friday, respectively, they will not receive TBS treatment.

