##### Primary outcome measure

Response to treatment will be primarily defined as a ≥ 50% reduction in pre-treatment symptom severity as measured by the HRSD-17 score. Treatment remission will be defined as a HRSD-17 score ≤ 7. These definitions of treatment response and remission are based on recent literature assessing the effects of rTMS in individuals with depression [33, 37, 38, 91, 92].

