##### Secondary outcome measure

For secondary analyses response to treatment will be defined as a ≥ 50% reduction in pre-treatment symptom severity as measured by the mean 16-item Quick Inventory of Depressive Symptoms–self report (QIDS-SR_16_) score and Montgomery–Asberg Depression Rating Scale (MADRS). Remission will be defined as a QIDS-SR_16_ score of ≤ 6 and a MADRS score < 12. Additionally, other secondary outcomes will include effect of treatment on anxiety (Beck Anxiety Inventory), symptoms of mania (Young Mania Rating Scale, Altman Self-Rating Mania Scale), quality of life (Quality of Life Enjoyment and Satisfaction Questionnaire), symptoms of post-traumatic stress disorder (Post-traumatic Stress Disorder Checklist for DSM-5), and well-being (Short Warwick Edinburgh Mental Well-Being Scale).

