### Effectiveness of TBS treatment

Secondarily, the effectiveness of both unilateral and bilateral TBS as well as their difference on treating MDD will be investigated with generalized linear mixed models with treatment groups (unilateral vs bilateral TBS) as between-subjects factor, and outcome measures (clinical scores, neurophysiological measures) as within-subject factors. The main effects of Time (pre, post) and Time X Group (unilateral vs bilateral TBS) interaction will be investigated, and Bonferroni-adjusted pairwise comparisons will be performed to determine statistically significant within- and between-subjects differences. This analysis take into account missing data, avoiding the use of additional methods such as multiple imputations. The binominal outcomes will also be examined using Chi-Squared tests, and the difference in proportion rates between the groups will be reported (e.g., Groups: bilateral vs unilateral TBS, and outcome: % of response/remission rate identified as “yes” and “no” as per HRSD-17 ≤ 50% reduction from the baseline score [37, 43, 106]. If the sample size and their demographics allow for group stratification based on age groups, biological sex and gender, and the presence/absence of comorbidities, we will conduct additional between-subject analyses to compare groups.

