### Predictors of treatment response

Exploratory relationships across outcome measures will be investigated using Pearson’s or Spearman’s correlation coefficients for normal and non-normal distributed data, respectively. Specifically, relationships between baseline levels of neurotransmitters, cortical excitability, and capacity of plasticity (rsfMRI and MRS, TMS, and TMS-EEG, respectively) and the degree of change (∆ pre-post treatment) in the assessed clinical outcomes will be performed to identify potential neurobiological predictors of response to treatment. As well, to provide some insight on possible neurobiological mechanisms involved in response to treatment, correlation analyses will be conducted between the degree of change (∆ pre-post treatment) in cortical plasticity (TMS-EEG) and clinical treatment response (e.g., HRSD-17). Additionally, regression analyses will be performed to predict response to treatment (e.g., “responders” and “non-responders”, and HRSD-17) with the neurobiological outcomes (MRI, TMS, TMS-EEG) entered as predicting variables. We will include demographics (e.g., age, sex, levels of education, amount of benzodiazepines being taken, employment status (measure of functionality), baseline HRSD-17 (MDD symptom severity), baseline BAI anxiety, degree of resistance to pharmacotherapy, etc.) as controlling variables. To investigate predictors within each treatment group, the correlations and regression analyses will be performed separately for each group and/or with groups entered as predicting variables. A Receiver Operating Characteristic (ROC) curve analysis will be performed to investigate the ability of significant predictors to classify response to treatment (achieved remission, "yes" or "no", based on ≥ 50% reduction from baseline HRSD-17 score; dependent variable). The area under the ROC curve with 95% CI will be investigated and the ‘cut-off point’ best classifying remission and its respective sensitivity and specificity percentage values will be identified.

Biological sex will be considered during analyses. Biological sex (male, female) will be inputted as predicting outcome variables (dependent) during regression analysis predicting the independent variables. As well, differences in treatment response and neurophysiological measures between the two biological sexes will be explored using independent t-tests.

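### Two secondary or exploratory analyses classify response and remission by rules that contradict the protocol's own definitions

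*Protocol article*

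**What the plan says.** The definitions stand in the protocol article under Primary outcome measure: "Response to treatment will be primarily defined as a ≥ 50% reduction in pre-treatment symptom severity as measured by the HRSD-17 score", and "Treatment remission will be defined as a HRSD-17 score ≤ 7". The text on treatment flow under Study design and overview agrees. It treats a score above 7 as non-remission, and it describes non-response in the same direction: "Participants who do not respond to treatment (i.e., < 50% decrease in pre-treatment HRSD-17 score".

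Two parts of Data analysis state something else.

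- Effectiveness of TBS treatment: the proportions for response and remission, compared between arms by chi-squared tests, are split into yes and no by a single criterion, "HRSD-17 ≤ 50% reduction from the baseline score".
- Predictors of treatment response: the ROC outcome is introduced as response, then named as achieved remission, then defined as "based on ≥ 50% reduction from baseline HRSD-17 score; dependent variable". The analysis goes on to seek the cut-off "best classifying remission and its respective sensitivity and specificity percentage values".

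**The concern.** The chi-squared criterion has two faults. Its inequality points the wrong way for response, since participants who are unchanged or worse satisfy it and those who improve by more than half do not. It also serves for remission, which the protocol defines by an absolute score and not by percentage change.

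The ROC analysis has the right inequality for response but attaches the name of the other outcome. A published cut-off, sensitivity and specificity for remission would then describe response.

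What is at stake is the responder table and the interpretation of the biomarker results. The chi-squared paragraph is where the article sets out the between-arm comparison of response and remission proportions. The Discussion says the biomarkers of response are meant to help select participants for TBS in clinical settings.

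**Working it through.** **Inputs.** Response: reduction of at least 50% (Primary outcome measure). Remission: HRSD-17 of 7 or less (same section). Entry: HRSD-17 of 15 or more (Table 2). Chi-squared rule: reduction of at most 50%. ROC rule: reduction of at least 50%, labelled remission. The document gives no figure that depends on these rules, so there is none to reproduce.

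**Rules as final scores.** With baseline b and final score s, the reduction is (b − s)/b.

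- Response: (b − s)/b ≥ 0.5, so s ≤ b/2.
- Chi-squared rule, read literally: (b − s)/b ≤ 0.5, so s ≥ b/2.
- Remission: s ≤ 7.

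**Response against the literal chi-squared rule.** The two agree only at s = b/2 exactly. Otherwise each is the complement of the other. Ignoring those ties, assumed true response rates of 50% and 40% become 100 − 50 = 50% and 100 − 40 = 60%. The difference goes from +10 to −10 percentage points.

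**Remission against the literal chi-squared rule.** At entry b ≥ 15, so b/2 ≥ 7.5. A remitter has s ≤ 7, which is below b/2, so no remitter can be a yes. In the extreme case, b = 15 and s = 7, the reduction is 8/15 = 53%. This also shows that every remitter is a responder.

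**Remission against the ROC rule.** Scores are whole numbers.

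| Baseline | ROC rule met at | Remission at | Called remission but above 7 |
|---|---|---|---|
| 15 | 7 or less | 7 or less | none |
| 16 | 8 or less | 7 or less | 8 |
| 20 | 10 or less | 7 or less | 8 to 10 |
| 24 | 12 or less | 7 or less | 8 to 12 |
| 30 | 15 or less | 7 or less | 8 to 15 |

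The rules coincide only at a baseline of 15, the lowest that is eligible. Table 3 places HRSD-17 scores of 8 to 13 in the mild depression band.

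**Illustration of size.** This rests on assumed distributions, not on the document: baseline mean 23, SD 4.5, restricted to 15 or more; percentage reduction with SD 30 and mean 35, 45 or 55.

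| Mean reduction | True response | Literal chi-squared yes | True remission | ROC remission with score above 7 |
|---|---|---|---|---|
| 35% | 32% | 70% | 15% | 53% |
| 45% | 45% | 58% | 24% | 47% |
| 55% | 58% | 45% | 35% | 40% |

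The last column is a share of those meeting the ROC rule. True response and the literal yes rate add to slightly more than 100% because participants at exactly 50% satisfy both (for example 32 + 70 = 102, or 2.6% before rounding).

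**The case against.** The strongest reply is that the chi-squared wording is a slip that the rest of the document resolves. Primary outcome measure, the discharge rule and the ROC paragraph all run the other way. The Sample size section describes a cited trial by a reduction of at least 50%, and the chi-squared sentence cites that same trial. The rule sits in an example in parentheses, and a score of at most 50% of baseline is a natural guess at what was meant. Swapping yes and no also leaves the chi-squared statistic for response essentially unchanged; only the labels and the sign of the reported difference move.

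Most of this stands, so an inverted responder table is a risk of following the text literally, not an expected result. It does not rescue remission. On the charitable reading, remission still takes the response rule, and its test would repeat the response test. The remission rule has to be brought in from another section.

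For the ROC analysis, the reply is that the subsection is about response, the operational rule is explicit, and only a word is wrong. That is fair, but the word appears both in the outcome and in the cut-off to be reported, so the text does not settle which outcome is intended.

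A reader might also infer that remission on the QIDS-SR16 is set wrongly. The Secondary outcome measure section gives a QIDS-SR16 "score of ≤ 6 and a MADRS score < 12", while Table 3 labels the QIDS-SR16 bands "0–5, no depression; 6–10, mild depression", so a score of 6 is both remission and mild depression. The documents do not support calling this an error. Nothing in them ties remission to the lowest severity band. The MADRS rule departs from its own band by more, since scores of 7 to 11 count as remission and as mild. Nor do the documents show that either QIDS-SR16 cut-off is wrong.

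**Conclusion.** The point holds for two stated rules. The chi-squared criterion contradicts the definition of response in direction and gives remission no rule of its own. The ROC analysis puts a remission label on the response rule. These contradictions follow from the text and the entry criterion alone. The 50% versus 40% example and the 40 to 53% of misnamed remitters rest on assumed inputs.

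Severity is moderate. A reader might infer that the main result is compromised, but the primary analysis is an ANCOVA on the continuous final HRSD-17 score, and neither it nor the calculated sample size of 158 uses these rules. The chi-squared tests are secondary, and the ROC analysis belongs to the work on predictors of response.

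**What to change.** In Effectiveness of TBS treatment, replace the single criterion with two separate binary outcomes, each with its own between-arm comparison: response as a reduction of at least 50% from baseline HRSD-17, and remission as HRSD-17 of 7 or less.

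In Predictors of treatment response, name one ROC outcome and use its matching rule from Primary outcome measure. If both are wanted, report two ROC analyses under their correct labels.

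Make both changes before unblinding, so that the choice of rule cannot be challenged as made after the results were seen. They are wording corrections that need no new data and cost no power.

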### Predictors of treatment response

Exploratory relationships across outcome measures will be investigated using Pearson’s or Spearman’s correlation coefficients for normal and non-normal distributed data, respectively. Specifically, relationships between baseline levels of neurotransmitters, cortical excitability, and capacity of plasticity (rsfMRI and MRS, TMS, and TMS-EEG, respectively) and the degree of change (∆ pre-post treatment) in the assessed clinical outcomes will be performed to identify potential neurobiological predictors of response to treatment. As well, to provide some insight on possible neurobiological mechanisms involved in response to treatment, correlation analyses will be conducted between the degree of change (∆ pre-post treatment) in cortical plasticity (TMS-EEG) and clinical treatment response (e.g., HRSD-17). Additionally, regression analyses will be performed to predict response to treatment (e.g., “responders” and “non-responders”, and HRSD-17) with the neurobiological outcomes (MRI, TMS, TMS-EEG) entered as predicting variables. We will include demographics (e.g., age, sex, levels of education, amount of benzodiazepines being taken, employment status (measure of functionality), baseline HRSD-17 (MDD symptom severity), baseline BAI anxiety, degree of resistance to pharmacotherapy, etc.) as controlling variables. To investigate predictors within each treatment group, the correlations and regression analyses will be performed separately for each group and/or with groups entered as predicting variables. A Receiver Operating Characteristic (ROC) curve analysis will be performed to investigate the ability of significant predictors to classify response to treatment (achieved remission, "yes" or "no", based on ≥ 50% reduction from baseline HRSD-17 score; dependent variable). The area under the ROC curve with 95% CI will be investigated and the ‘cut-off point’ best classifying remission and its respective sensitivity and specificity percentage values will be identified.

Biological sex will be considered during analyses. Biological sex (male, female) will be inputted as predicting outcome variables (dependent) during regression analysis predicting the independent variables. As well, differences in treatment response and neurophysiological measures between the two biological sexes will be explored using independent t-tests.

Interim analyses of TMS, TMS-EEG, MRI, and clinical data will be conducted to further explore biomarkers of depression and comorbid disorders and mechanisms of action of TBS. These will further enhance the impact of the study and leverage the large dataset collected. These analyses will be blinded to treatment allocation and trial outcome (e.g., without dividing response or remission rates by group) until the end of the trial. Objective and hypotheses will be guided by existing knowledge and new discoveries in the field of non-invasive brain stimulation and psychiatry.

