Following referral and screening (see Table 2 for detailed inclusion/exclusion criteria), written consent to participate will be obtained by trained research personnel after the participant has had the study explained to them in full and had the opportunity to ask questions. Participants will then be assessed for demographics and several clinical and neurophysiological outcomes (Fig. 2A). All demographic, clinical, and neurophysiological assessments throughout the study will be administered by trained research personnel. The clinical and neurophysiological outcome measures collected throughout the study (their description, assessment timepoint, and rationale for inclusion) are described in detail in Tables 3 and 4, respectively.

**Table 2 Tab2:** Study inclusion and exclusion criteria

Inclusion Criteria	• Voluntary and competent to consent to the study • Able to communicate/read in English or French • Primary and/or predominant diagnosis of MDE without psychotic features confirmed by the Mini-International Neuropsychiatric Interview • Depressive symptoms not improving after ≥ 1 adequate doses of antidepressant trials in the current depressive episode • Moderate symptoms in the current depressive episode as indexed by a score of ≥ 15 on the HRSD-17 • Have been referred to rTMS treatment by their treating physician, and took a free and informed decision to follow this treatment • Are able to adhere to the treatment schedule • Have received a stable medication (including prescribed cannabis) or psychotherapy regiment for at least four weeks prior to entering the study • Have an education-adjusted score of ≥ 24 on the Mini-Mental State Evaluation if ≥ 65 years-old • Negative urine test for use of recreational drugs and/or pregnancy (tested at baseline)

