**Single and Paired-Pulse TMS**	RMT	Assesses cortical excitability via indirect activation of cortical interneurons (I-wave)	M1 (bilaterally)	Used to normalize the following TMS experiments (e.g., % of RMT)
	AMT	Cortical excitability via direct activation of corticospinal tract neurons (D-wave)	M1 (bilaterally)	Used to normalize the TBS treatment intensity (e.g., % of AMT)
	MEP Amplitude	Capacity of the corticospinal tract in recruiting neurons from faster temporospatial summation at cortico-motoneuronal synapses. Reflects glutamatergic (NMDA- and AMPA-receptor) activity	Left M1	Used as unconditioned MEP (i.e., test MEP), to calculate degree of inhibition during paired-pulse experiments (e.g., degree of inhibition = conditioned/unconditioned MEP)
	SICI	Short-interval intracortical inhibition primarily influenced by GABA_A_-receptor activity	Left M1	To investigate TMS biomarkers of treatment response examined with correlation analysis between baseline TMS and pre-post changes in clinical measures
	LICI	Long-interval intracortical inhibition primarily influenced by GABA_B_-receptor activity	Left M1	
	ICF	Intracortical facilitation primarily influenced by glutamatergic (NMDA- and AMPA-receptor) activity	Left M1	
**TMS-EEG**	TEP and ERSP	Assesses trans-synaptic activation of local and distal cortical networks mediated by excitatory and inhibitory cortical circuitry	TMS performed on the left and right DLPFC (120% of RMT) and TEP/ERSP are recorded from the DLPFC (primarily) and whole brain (exploratorily)	To investigate TMS-EEG biomarkers of treatment response, examined with correlation analysis between baseline TEPs/ERSPs and pre-post changes in clinical measures. To investigate cortical changes from treatment, examined with repeated-measures analysis [pre- vs post initial treatment (week 4, or week 6 for non-remitters), vs post maintenance phase (e.g., final week (week 24)]
**MRI**	Structural MRI	Assesses anatomy and morphology of CNS structures	Whole brain	To be uploaded into the neuronavigation software to assist with the location and targeting of the M1 and DLPFC during TMS assessments and TBS treatment, respectively (MRI-assisted TMS)
	MRS	Availability of neurotransmitters within the CNS (GABA and Glutamate)	Bilateral ACC	To investigate biomarkers of treatment response, examined with correlation analysis between baseline values and pre-post changes in clinical measures

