
For instance, a previous TMS-EEG study has shown higher intracortical inhibition (e.g., N45 and N100 amplitude) in the DLPFC of individuals with a diagnosis of MDD in comparison to healthy controls. N45 amplitudes were also predictive of a higher degree of depression [64]. By looking at other events of TEPs (e.g., P60, a biomarker of intracortical excitation) these authors also reported higher excitation and an excitation/inhibition imbalance in the DLPFC of individuals with a diagnosis of MDD in comparison to healthy controls, and a further abnormal lack of association between excitation and inhibition in MDD, an association that is present in the healthy brain [64]. Abnormalities in neurophysiological features in MDD have shown to be associated with diminished capacity for neuroplasticity, which in turn, has been associated with a higher degree of MDD symptoms and relapses [128]. Ge et. al (2022) showed that the first treatment session of rTMS-inhibitory stimulation delivered to the right DLPFC induced acute widespread changes in functional connectivity measured by fMRI (i.e., TMS-fMRI) [134]. Interestingly, these authors reported that this first acute rTMS-induced plasticity response, but not resting state fMRI, was predictive of clinical outcomes (determined by MADRS scores) collected 4 weeks later, after cessation of daily rTMS treatment [134]. Most recently, in a subset of MDD participants who completed the Blumberger trial, Strafella, et al. (2023) reported that both iTBS and HF-rTMS reduced N100. Interestingly, participants who responded to treatment had higher baseline N100 and higher N45 post treatment when compared to non-responders [135]. Taken together, these findings provide support for the link between the neurophysiological effects of TBS and treatment effectiveness. Therefore, we will use TMS-EEG to investigate trans-synaptic activation of local and distal cortical networks mediated by excitatory and inhibitory cortical circuitry [48]. One novelty of our TMS-EEG method is the additional investigation during treatment, which has never done before and could complement the existing pre-post findings and could identify new neurophysiological markers of TBS response. As well, like Ge et. al (2022) we will assess the widespread TBS treatment-induced plasticity throughout treatment (see Table 3 for time points) [134]. This will be done to investigate whether the first treatment-induced plasticity is predictive of outcomes and whether the longer-term treatment can restore the diminished plasticity in MDD. As well, we will include additional neuroimaging techniques assessed during baseline, MRS and resting state fMRI, to investigate the availability of neurotransmitters (GABA and glutamate) within the ACC and connectivity between CNS structures, respectively. Both of these techniques are popular in MDD research and have shown to be sensitive to identifying abnormal neurophysiological features in MDD (for review see [136, 137]).

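### Correlating baseline markers with pre-post change, unadjusted for the baseline score, can flag mere severity markers; the baseline-adjusted model should decide what counts as a predictor and what enters the ROC analysis

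*Protocol article*

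**What the plan says.** The section Predictors of treatment response in the protocol article describes three steps.

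1. **Correlations.** "Exploratory relationships across outcome measures will be investigated using Pearson’s or Spearman’s correlation coefficients". Correlations of baseline MRS, resting-state fMRI, TMS and TMS-EEG values with the degree of pre-post change "in the assessed clinical outcomes will be performed to identify potential neurobiological predictors of response to treatment". No covariate is named for this step.
2. **Regressions.** Additionally, "regression analyses will be performed to predict response to treatment", with the MRI, TMS and TMS-EEG markers as predictors. Outcomes are responder status and HRSD-17. Baseline HRSD-17 and baseline BAI are among the listed controlling variables.
3. **ROC analysis.** Significant predictors are carried into an ROC analysis with a cut-off. The text does not say which of the first two steps establishes significance.

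Table 4 gives the reason for collecting each technique. For single- and paired-pulse TMS it is a "correlation analysis between baseline TMS and pre-post changes in clinical measures". For MRS and functional MRI it is "To investigate biomarkers of treatment response, examined with correlation analysis between baseline values and pre-post changes in clinical measures". The TMS-EEG row has the same wording for baseline TEPs/ERSPs and adds a repeated-measures analysis for cortical change. No row mentions regression for biomarkers of response.

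The Abstract and the Sample size section both name regression as the analysis of biomarkers or predictors of response.

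**The concern.** The correlation step tests whether a marker is unrelated to final minus baseline. The question of interest is whether the marker says anything about outcome beyond how ill the patient was at entry. These differ whenever the slope of final on baseline is not 1. With a slope below 1, more severely ill patients show larger raw falls, and any marker tied to severity inherits that association.

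The article gives a reason to take this seriously for at least one marker. In the Discussion it reports from a cited study that "N45 amplitudes were also predictive of a higher degree of depression", and baseline TEPs are among the Table 4 correlations. The direction could also mislead: Table 1 expects higher severity to go with poorer outcome, yet a severity marker would appear here as a predictor of larger improvement.

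At stake is whether a severity marker could be listed as a potential predictor of TBS response and be given a cut-off, while the adjusted regression on the same data gives it no support.

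**Working it through.** **The plan's own predictor figure.** The Sample size section gives n = 30–39 for a regression with 3–6 variables, R² = 0.30, power 0.80 and α = 0.05. With f² = 0.30/0.70 = 0.43 and the overall F test (noncentrality f²·N, degrees of freedom p and N − p − 1), the required N is 30, 33, 36 and 39 for p = 3, 4, 5 and 6. The figure reproduces. It sizes the regression, not the correlations.

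**Inputs from the article.** Two-sided α = 0.05; n = 158 (79 per arm), maximum 256.

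**Assumptions (not in the article).** Marker–baseline correlation ρ; pre-post correlation r of the clinical score; SDs at baseline and final, with ratio k = final SD / baseline SD. The marker relates to the final score only through baseline, so it has no predictive value of its own.

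**Induced correlation.** With change = baseline − final,

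corr(marker, change) = ρ(1 − rk) / √(1 + k² − 2rk).

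The product rk is the slope of final on baseline, so the induced correlation vanishes at slope 1.

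**Worked case.** ρ = 0.3, r = 0.5, k = 1: 0.3 × 0.5 / √1 = 0.15. On the Fisher scale, atanh(0.15) × √(158 − 3) = 0.151 × 12.45 = 1.88. The chance of exceeding ±1.96 is 47%, against a nominal 5%.

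**Other settings** (chance of p < 0.05, same formulae; each range is ρ = 0.3 to ρ = 0.5):

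| Baseline SD, final SD | r | Slope | n = 79 | n = 158 |
|---|---|---|---|---|
| 5, 5 | 0.5 | 0.50 | 26–60% | 47–89% |
| 5, 6 | 0.35 | 0.42 | 23–53% | 41–83% |
| 4, 7 | 0.35 | 0.61 | 9–17% | 14–30% |
| 4, 7 | 0.5 | 0.88 | 6–7% | 6–8% |

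With ρ between 0.2 and 0.4 and r between 0.3 and 0.7 at n = 158, the range is 16–85% at k = 1 and 5–44% at k = 1.5. It is close to 5% in the latter case when r = 0.7 (slope 1.05). In the worked case the rate rises to 67% at n = 256.

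**With baseline in the model.** Simulation (4,000 runs per setting; n = 79, 158 and 256) of change regressed on marker plus baseline gives 4.6–5.6% rejections. Regressing the final score instead gives the same marker coefficient and test, because baseline is a covariate in both.

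**How far the planned regressions already cover this.** They cover HRSD-17, because baseline HRSD-17 is a listed control. For MADRS and QIDS-SR, which are secondary outcomes and fall within the clinical outcomes assessed, own-scale baseline is not named. The section lists at least eight controls (age, sex, education, benzodiazepine use, employment, baseline HRSD-17, baseline BAI, drug resistance), while the regression was sized for 3–6 variables in all. The text does not say which controls are kept if the list has to be cut.

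**The case against.** The strongest reply is that the protocol already has the right analysis. The Abstract and the Sample size section identify regression as the predictor analysis, and those regressions control for baseline HRSD-17. The correlations are labelled exploratory and look only for potential predictors; Table 4 summarises techniques and sets no decision rule. This stands. A reader might infer that markers will be declared predictors on the raw correlation alone, but no sentence says so.

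A reader might also infer that baseline N45 is a hypothesised predictor. Table 1 does not support that: its TMS-EEG hypothesis concerns the change after session 1, and only the GABA/glutamate and connectivity hypotheses concern baseline levels. N45 enters through the Table 4 correlations, and its link to severity is one cited study's result, given without a coefficient.

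The size is also open to challenge, and fairly.

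- The entry rule, "Moderate symptoms in the current depressive episode as indexed by a score of ≥ 15 on the HRSD-17", restricts the baseline range. With an assumed untruncated mean of 18–20 and SD of 5–6, a cut at 15 lowers a marker–severity correlation of 0.3 to about 0.2 and one of 0.5 to about 0.4.
- The article does not say whether change is absolute or a percentage. With percentage change and assumed means falling from 23 to 10–13, the first three rows of the table drop at n = 158 to about 5–10%, while the fourth rises to about 12% or more.

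So the amount, and even which settings suffer, depends on values and a definition the article does not give. The mechanism does not.

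Finally, an article may leave covariate detail to the analysis plan. That would answer a complaint about omission. Here, however, a method is stated, both in the text and in Table 4, and the point concerns that method.

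**Conclusion.** The concern holds in a limited form. The stated correlation step tests the wrong null for identifying predictors of response, and under plausible assumptions it can flag a pure severity marker far above 5%: 47% in the worked case at n = 158, but close to 5% when the slope of final on baseline nears 1. These figures assume absolute change, approximate normality and the correlations and SDs listed; none comes from the article.

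The planned baseline-adjusted regression removes the artefact for HRSD-17. Three gaps remain: Table 4 names only the correlations for biomarkers of response; own-scale baseline is not named as a control for MADRS or QIDS-SR; and the ROC analysis takes its predictors from an unspecified step. The primary comparison of the two arms is unaffected. This is a correction to the wording of the biomarker analysis, worth making because it is nearly free.

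**What to change.** In Predictors of treatment response and in Table 4, state that a marker counts as a predictor, and enters the ROC analysis, on the basis of the baseline-adjusted model: final clinical score on the marker, adjusted for the baseline value of the same scale and for arm. A partial correlation, rank-based where data are not normal, is an equivalent option. Keep own-scale baseline and arm in the model whatever other controls are dropped. Retain the raw marker–change correlations, if wanted, as descriptive only.

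The cost is one or two degrees of freedom and possibly fewer nominally significant markers. Baseline scores are already collected, so no new data or visits are needed.
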